**Figure 2. fig2-15347354251361464:**
[figure not shown]
Timeline of data collection. T1, Time-point 1, T2, Time-point 2. Antiemetic treatment types: A, standard care, no acupuncture; B, sham acupuncture; C; verum acupuncture. Communication styles: 1, neutral communication style; 2, positive communication style. Objective physiological measures: heart rate, blood pressure, salivary cortisol. Repeatedly during the study period, also co-occurring symptoms, and co-interventions such as medications and self-care are self-registered.

### Study Procedure

The intervention therapist conducts the treatment procedure twice within the studied chemotherapy session. The first time (T1), illustrated with 1/2 + A/B/C in Figure 2, is conducted for 20 minutes (irrespective of verum or sham acupuncture is given) immediately pre intravenous chemotherapy. The second time (T2), also illustrated with 1/2 + A/B/C in Figure 2, is conducted for 20 minutes (irrespective of verum or sham acupuncture is given) immediately post intravenous chemotherapy. Twenty to 30 minutes is a common duration for a single acupuncture session in clinical practice.^
23
^ If the patient’s chemotherapy session lasts for 2 consecutive days, the intervention takes place on day 1. The whole study procedure lasts from the day before intervention day until day 10 after the very last chemotherapy session. Figure 2 presents the study procedure timeline.

### The Intervention Therapists Delivering the Communication Model and the Acupuncture Types

The therapists delivering the communication styles and the antiemetic acupuncture types (the intervention therapists) are registered physiotherapists with professional experience and education in acupuncture. Before beginning as an intervention therapist for the present study, they are introduced to the standardized treatment protocol for a full working day (about 8 hours) by the project manager (the last author). They then continue to practice until they feel comfortable and experienced in implementing the standardized study protocol. Prior to the study, some of the intervention therapists have also practiced the communication model with 30 study participants each, during the preceding procedure validating the communication model.^
51
^ The intervention therapists respond to a study-specific questionnaire regarding years in the profession and their own experience of and belief in acupuncture effects prior to joining the study. The treatment expectancy measure,^
56
^ ask: “Do you believe that the treatment you are going to give is effective against nausea and vomiting?” rated on a 100 mm VAS anchored with 0 (“I don’t believe at all that it’s effective”) and 100 (“I completely believe that it’s effective”).

### The Communication Model Involving 2 Communication Styles

To manipulate the non-specific component treatment expectations during treatments,^
57
^ the intervention therapist applies a previously validated communication model,^
51
^ inspired by Kaptchuk et al,^
47
^ covering 2 verbal communication styles, where the non-verbal communication (facial expressions and body language)^48,49^ is in line with the verbal communication.

The neutral communication style: During treatment Type B-C at T1 and T2, the intervention therapist communicates at least 3 out of several neutral statements such as: “Many acupuncture studies have shown different results regarding whether or not acupuncture treatment prevents and relieves nausea,” “We don’t really know if acupuncture is a good method for producing antiemetic effects; thus we need to perform this study,” “We cannot know whether you will experience antiemetic effects of the acupuncture treatment; I have treated persons who felt differently about it.” During treatment Type A, the neutral communication is to be as similar to standard care as possible. The intervention therapist just quickly comes around, explains the data collection procedure, but does not talk explicitly about expected antiemetic effects.The positive communication style: The intervention therapist communicates at least 3 of several positive statements during treatment Type B-C such as: “Many acupuncture studies have shown that acupuncture is effective compared to medication alone,” “Patients receiving acupuncture often feel that the treatment prevents and relieves nausea,” and “I have had positive effects preventing nausea using this treatment before.” During treatment Type A, the intervention therapist communicates things such as: “Many studies show that antiemetics are highly effective in preventing and relieving nausea,” “Many patients who receive the antiemetic medication you are receiving feel that the medication prevents and relieves nausea,” and “I have met many patients who have had good effects from their antiemetics.”

The positive or neutral communication is to permeate the entire intervention. The intervention therapists are instructed to find a personal, natural way to deliver the content of the statements described above, rather than repeating them verbatim.

### The Antiemetic Treatment Involving 3 Treatment Types

When undergoing A, B, or C, the patient (not undressed) is in the position for receiving intravenous chemotherapy, that is, sitting relaxed or lying.

A) The standard care group receives no acupuncture. Patients receive only antiemetics, according to the oncology departments’ standard care routines (at doses according to the Swedish Medicine Information Engine; http://www.fass.se) based on international guidelines,^1
[Bibr bibr2-15347354251361464][Bibr bibr3-15347354251361464]-4^ adapted to individual patients^
17
^ by their oncologists.B) The intervention therapist administers *sham acupuncture* for 20 minutes with the telescopic non-penetrating Park et al’s sham needle (blunt needles diameter 0.25 × length 45 mm)^
58
^ bilaterally to a non-acupuncture point 1 body-inch radial to the PC6 point, which is located 4 body-inches proximal to the wrist. Park’s sham needle credibly blinds patients.^
59
^ It looks identical to a real needle but glides upward into its handle, giving the illusion of penetration.^
58
^ A marking tube, identical for both acupuncture types, holds the sham needle in place (the marking tube is used in both allocation groups). The intervention therapist manipulates the sham needle a few seconds 3 times per session until the needle touches the skin, but no “needle sensation” occurs, and then lifts the needles up from the skin. Except for when placing and manipulating the needle, the sham needle thus puts no pressure on the skin, like the procedure used in previous studies.^27,37,51^C) The intervention therapist administers western medicine *verum acupuncture* (sharp needles diameter 0.25 × length 40 mm) for 20 minutes bilaterally to the acupuncture point pericardium six (PC6). PC6 is located between the tendons of palmaris longus and flexor carpii radialis at 2 body-inches (1 body-inch approximately 1.5 cm) proximal to the wrist at 0.5 body-inch depth. The therapist manually manipulates the needles 3 times per treatment T1 and T2 by rotating, thrusting, or lifting the needles. When patients report a sense of numbness or soreness and the therapist observes a minimal muscular contraction around the needle, that is, the “needle sensation.”^
60
^

### Data Collection

Data are being collected at multiple time points (see Figure 2): first, at baseline—the day before the designated chemotherapy session in which the patient participates in the study; then daily for 10 consecutive days, with explicit follow-ups on day 5 and day 10; and finally, 10 days after completion of the patient’s entire chemotherapy regimen (which typically lasts about 6 months according to the individual care plan). The SPIRIT^
54
^
Figure 3 gives an overview of the data collection.

**Figure 3. fig3-15347354251361464:**
[figure not shown]
Schedule of enrollment, intervention and assessment (SPIRIT). ^
1
^Measured immediately post intervention. ^
2
^Therapist data were only collected once, preceding study involvement. FACT-G: Functional Assessment of Cancer Therapy-General; QoL: quality of life; EQ-5D-3L: Euroqol 5 dimensions, 3 levels; EQ-VAS: Euroqol Visual Analog Scale; NBHW-PAI: National Board of Health and Welfare’s Physical Activity Indicator Questions.

Independent of patients’ cancer care, the study coordinator at each department sends the baseline questionnaire and the daily nausea and vomiting measure to patients by post or e-mail, according to the preferences patients expressed during the telephone call when study information was provided. The intervention therapists give patients the 10-day follow-up questionnaire and the completion questionnaire directly after conclusion of the study intervention, clearly stating that “these questionnaires come from the evaluator, and I will not be aware of your answers.” Patients may answer the different questionnaires using either “pen and paper” or the study’s digital web questionnaires, according to their own preferences. The study information ensures patients that their responses (marked by an identification code instead of any personal information) will not be managed by the cancer care personnel, only by the independent study evaluator.

About 1 to 2 weeks after an expected response, the study coordinator sends a gentle reminder through the post to those who have not yet responded, and after responding to the completion questionnaire, patients receive a letter, sent via post, expressing our gratitude for their participation. Figure 3 presents the measurements described below.

Medical record clinical data: Research nurses of the oncology departments collect data from patients’ medical records regarding cancer diagnosis, disease-specific variables, types, doses and frequency of chemotherapy, and if the patient was chemotherapy-naïve or not when participating in the study. Data on the types and doses of prophylactic antiemetics given to the patients are also collected, for the entire chemotherapy period.

Self-reported descriptive data: On a baseline questionnaire, patients supply sociodemographic data (eg, sex, age, level of education, profession), clinical data (eg, comorbidities, disease-specific variables, medications), data on previous experience of and belief in acupuncture effects,^
22
^ data on previous nausea experiences in their lives and specifically when undergoing cancer therapy, self-predicted risk for nausea,^
36
^ and data regarding therapeutic alliance, for example, to which extent the patient trusts the therapist to be able to help him/her.^
61
^

Data on nausea and vomiting: Patients complete a measure of nausea and vomiting^
7
^ daily for 10 days, answering questions about the primary outcome (nausea intensity) and the secondary outcomes (nausea occurrence, duration of nausea, vomiting episodes, and consumption of antiemetics). This measure asks the following questions with reference to the past 24 hours: “Have you experienced nausea?” (“No” / “Yes”); “How intense was the nausea?” A 100 mm VAS with verbal anchors “No nausea” and “Worst possible nausea” is used. The accumulated duration (in minutes) of nausea within the past 24 hours is registered. Patients also respond to the questions: “Have you vomited?” (“No”/“Yes”), “How many episodes?” (number of episodes is given), and “Have you consumed rescue antiemetics?” (“No”/“Yes”). They are asked to: “Please detail agent, dose and frequency of each antiemetic agent used.” Also, other kinds of nausea and vomiting-related care consumption is self-registered. Burden is asked for and registered on 2 separate 100-mm VAS: “Did the nausea negatively affect your daily life?.” The same question is posed regarding vomiting, both anchored with 0 (“Not affected at all”) and “100” (“Affected in the worst possible way”; Figure 2).

Expectations data: Patients rate their treatment expectations daily for 10 days, using a valid expectancy measure,^
56
^ “Do you believe that the treatment you are going to receive is effective for nausea and vomiting?” This is measured using a 100 mm VAS anchored with 0 (“I don’t believe at all that it’s effective”) and 100 (“I completely believe that it’s effective”). Post-treatment, the question is written with the modified verb tenses “received” and “was.”

Treatment satisfaction data: On day 10 after the intervention, patients rate their interest in receiving future acupuncture treatment by answering the questions^
37
^ “If you should need similar chemotherapy in the future, would you be interested in receiving antiemetic acupuncture treatment?” (“Yes, completely interested,” “Yes, very interested,” “Yes, moderately interested,” “Yes, a little interested,” “No, not interested”), and “If you should experience other problems in the future that could be treated with acupuncture, would you be interested in receiving acupuncture treatment?” (“Yes, completely interested,” “Yes, very interested,” “Yes, moderately interested,” “Yes, a little interested,” “No, not interested”). After completion of the entire chemotherapy period, patients rate the self-perceived overall nausea intensity, and the burden of it, for the entire chemotherapy period,^
7
^ as well as the overall perceived effect of the antiemetic treatment,^
37
^ using 3 different 100 mm VAS anchored with 0 and 100 (labeled “No nausea” and “Worst possible nausea”; “No burden” and “Worst possible burden”; and “Not effective at all” and “Completely effective,” respectively).

QoL data: Patients repeatedly (Figure 2) respond to the Swedish version^
62
^ of Functional Assessment of Cancer Therapy—General (FACT-G).^
63
^ The 27-item FACT-G covers 4 domains on health-related QoL: physical wellbeing (7 items), social wellbeing (7 items), emotional wellbeing (6 items), and functional wellbeing (7 items), graded on a numerical rating scale from 0, “completely disagree” to 4, “completely agree.” Higher scores on the domains and the total score indicate better QoL. Patients also grade their health-related QoL on the Swedish version^
64
^ of the Euroqol-5 Dimensions-3 Levels (mobility, self-care, usual activities, pain/discomfort, anxiety/depression), and Euroqol-VAS, a 100 mm vertical scale anchored with 100, “best imaginable health state” and 0, “worst imaginable health state.”^
65
^ Further, responses are given to a single-item question regarding global QoL.^
66
^

Daily and physical activity data: Daily activities (often mentioned as “everyday activity,” or “activities of daily living”) the preceding week are assessed using 7-graded statements ranging from “I managed all my daily activities” to “I did not manage any of my daily activities.”^
67
^ Physical activity performance is assessed using widely used self-report questions^
68
^: “During a regular week, how much time do you spend exercising at a level that makes you short of breath, for example running, fitness class, or ball games?” (ie, vigorous activity), and “During the past week, how much time are you physically active in ways that are not exercise, for example walk, bicycling, or gardening?” (ie, moderately intensive activity). Patients answer the questions by adding together all activities lasting at least 10 minutes and choosing between categories, for example, “31-60 minutes.” At baseline, they register vigorous and moderate physical activity during a regular week, using the same questions regarding the current week.^
68
^ They report their work activity by self-reporting the percentage of sickness absence (0%, 25%, 50%, 75%, or 100% sick leave), which has good agreement with register-based data.^
69
^ Using a single-item question, potential fear of being active (kinesiophobia)^
70
^ is registered.

Objective physiological data: The intervention therapist measures patients’ heart rate (Beats Per Minute, BPM) and blood pressure (mm of mercury, mm/Hg) twice, using a digital upper arm blood pressure monitor twice (Figure 2). Patients place their left arm, which is relaxed, on the surface (with their palm up), and the intervention therapist positions the monitor approximately 2 cm above the elbow joint.

Patients provide saliva samples twice (Figure 2) for measuring cortisol concentrations, according to previously used standardized routines.^
71
^ They perform the first sampling procedure after resting during an introductory conversation and pre-chemotherapy preparations with the intervention therapist (approximately 10-15 minutes) immediately preceding their treatment A, B, or C, combined with communication style 1 or 2. They wet a cotton swab with saliva by moving the swab around in their mouth for 1 to 2 minutes, without eating, drinking, chewing gum, or using tobacco during this procedure. They then place the swab in a Salivette^®^ tube (Sarstedt, Nümbrecht, Germany). The patients perform the second sampling procedure according to the same standardized routine immediately after their treatment A, B, or C, combined with communication style 1 or 2.

The analyzer at the laboratory of each hospital at the study sites analyzes the samples using an enzyme immunoassay kit (Salimetrics LLC, USA). Regarding the precision of the measurements, the total coefficient of variation is 13.3% at 3.4 nmol/L and 6.3% at 29.4 nmol/L. The detection limit is 0.3 nmol/L. If the analyses cannot be done consecutively, the laboratory may store the samples at −20°C for up to 9 months.^
71
^ In the event of storage, the samples will be thawed at room temperature and centrifuged at 1500*g* before assay.

Treatment adherence, complications, and blinding data: At every treatment session, the intervention therapists register their adherence to the study protocol (eg, treated acupuncture points, number of needle stimulations, delivered verbal phrases). The intervention therapists register potential negative side-effects or complications occurring during the treatment sessions.

At the 10-day follow-up measure, patients respond in a binary fashion to a blinding measure^
59
^: “Do you think you have been treated with needles that have penetrated your skin, or do you think the needles have only been placed against the surface of your skin?” They also grade how certain they feel on the accuracy of their response: “Not sure at all, just guessed,” “fairly sure,” “entirely sure.” If patients have received standard care only, they choose the additional alternative “Not applicable, I did not receive any acupuncture treatment.” They respond to the question^
51
^: “During your chemotherapy session, you met an intervention therapist. Do you think you have received treatment from a therapist who emphasized the expected positive effects or one who did not?” This is measured using a 100 mm VAS anchored with 0, “Communicated very negative” and 100, “Communicated completely positive.” Patients in treatment type B-C grade their self-perceived needle-induced pain (“No/little/moderate/very painful”) and register potential side-effects of the acupuncture treatment.

Co-occurring symptoms, consumption of co-interventions: Patients repeatedly grade experience of co-occurring symptoms/problems, fatigue,^
72
^ sleeping quality,^
73
^ anxious and depressed mood,^
74
^ relaxation,^
51
^ pain and unpleasant symptoms (ie, neuropathy symptoms),^
75
^ wellbeing,^
37
^ eating capacity,^
76
^ and stool frequency.^
57
^ Since both symptoms and treatments may influence nausea and vomiting, QoL, and daily or physical activity levels, we include study-specific questions to determine whether participants are taking medications or other co-interventions beyond antiemetics and to describe their potential self-care strategies.

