### Sample Size

Participants will complete the study procedure during a single chemotherapy session, specifically, the next scheduled session following inclusion. The primary outcome is the mean intensity of nausea for the first 5 days, that is, the day of the intravenous chemotherapy session and the 4 following days of the studied chemotherapy session period. We performed an a priori sample size calculation, ensuring the study to be sufficiently powered. Based on previous research,^
15
^ we aimed to detect a clinically important difference of 10 millimeters (mm) using a 100 mm Visual Analog Scale (VAS) nausea measure between the positive and neutral communication group. Assuming a 2-sided alpha of .05 and statistical power of 80%, we estimated that 198 participants (99 per communication style group) would be required. The data analysis will be conducted according to intention to treat. To allow for a potential dropout rate of 20% between inclusion and the study procedure, the study will recruit up to 240 patients.

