Oncology nurses at the oncology departments are consecutively identifying patients scheduled for chemotherapy, asking if the patients are interested in receiving information about the study, and if they are, the nurses send study information by post. Next, the study coordinator of each department contacts the patients, providing the study information verbally and giving opportunities to ask questions. The written and verbal information states that patients will be randomized to receive antiemetics according to standard care routines or standard care combined with 1 of 2 types of acupuncture needling procedures: one that penetrates the skin and one where the needles are placed against the skin. Neither of the acupuncture needling procedures is described as a sham treatment. Further, the information states that the treatment types will be given using 2 types of “treatment procedures” performed by the intervention therapist, without any further specification, the goal being to prevent patients from knowing too much about the exact contents of the communication styles. Patients who agree to participate in the trial give their written informed consent.

Participants are scheduled to complete the study procedure during the chemotherapy session immediately following inclusion. However, certain exceptions to this plan may occur. The combination of chemotherapy agents varies according to each patient’s individual cancer treatment plan. If the next scheduled session involves only low-emetogenic agents (ie, no moderate-to-high emetogenicity), the study procedure will instead take place during the subsequent session. Practical considerations—such as treatment being administered at a different hospital or the intervention therapist being unavailable—may also necessitate postponing the study procedure to a later session. In these cases, participants will be involved in the study procedure during the next appropriate chemotherapy session. We will document the total number of chemotherapy sessions administered prior to the study session and record the emetogenicity levels of the agents used (see chapter Data collection, on medical record clinical data).

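### The 10-day questionnaire, which appears to name the concealed communication contrast, is handed to patients before any of the five primary-outcome days is complete

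*Protocol article*

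**What the plan says.** **Handover.** Data Collection (text under Figure 3): "The intervention therapists give patients the 10-day follow-up questionnaire and the completion questionnaire directly after conclusion of the study intervention". The baseline questionnaire and the daily nausea and vomiting measure take another route: the study coordinator sends them by post or e-mail. Patients may answer on paper or on the web.

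**End of the intervention.** Study Procedure: the second treatment "is conducted for 20 minutes (irrespective of verum or sham acupuncture is given) immediately post intravenous chemotherapy". When chemotherapy runs over two consecutive days, "the intervention takes place on day 1".

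**Primary outcome.** Sample Size: mean nausea intensity over "the day of the intravenous chemotherapy session and the 4 following days of the studied chemotherapy session period". Patients rate it themselves on a 100 mm VAS; according to Data Collection, "This measure asks the following questions with reference to the past 24 hours".

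**Content of the 10-day form.** The paragraph on adherence, complications and blinding opens: "At the 10-day follow-up measure, patients respond in a binary fashion to a blinding measure". It goes on to a second question, about the therapist: "Do you think you have received treatment from a therapist who emphasized the expected positive effects or one who did not". The answer is given on a VAS running from very negative to completely positive communication.

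**Concealment.** Recruitment of Patients says the information given to patients mentions two kinds of treatment procedure without specifying them, "the goal being to prevent patients from knowing too much about the exact contents of the communication styles". Randomization and Blinding states that patients are blinded to the communication allocation.

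**The concern.** The sample size is built on positive versus neutral communication, the outcome is a subjective self-rating, and treatment expectation is the hypothesized mediator, rated daily for 10 days. Each patient meets only one style and is not told that style is what varies between the two procedures. The question about the therapist supplies the missing contrast: it mentions both a therapist who stressed benefit and one who did not.

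A patient who sees it during the diary period could infer the manipulated factor and his or her own side of it. Someone in the neutral group might conclude that others were encouraged; someone in the positive group might discount what was said. Either could shift the expectation and nausea ratings while both are still being collected, and the two reactions need not bias the comparison in the same direction.

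**Working it through.** No arithmetic beyond counting days is needed. The point rests on setting the sections side by side.

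1. **When the form changes hands.** The second treatment follows the infusion and lasts 20 minutes (Study Procedure). The form is handed over straight after that (Data Collection), so handover falls on the chemotherapy day.
2. **Two-day sessions.** The intervention is still on the first day, so the form can be in hand before the second day of chemotherapy.
3. **The primary window.** It is the chemotherapy day plus the 4 days after it: 1 + 4 = 5 days (Sample Size). At handover the first day is still running, so completed days = 0 of 5. Part of the first day and all of the other four lie ahead.
4. **The mediator.** Expectation is rated daily for 10 days (Data Collection), so nearly all of its series also follows handover.
5. **Whether the item is in that form.** The paragraph begins by naming the 10-day follow-up measure, gives the needle question, and continues with what patients answer, including the therapist question. The past-tense wording of that question fits. This is the natural reading, but it is an inference: Figure 3 is not available, and its footnote refers to something measured immediately after the intervention without saying what.
6. **What the item adds to what patients know.** Recruitment of Patients leaves the two procedures unspecified. The therapist question identifies emphasis on positive effects as the dimension of interest. That is new information.
7. **Whether anything stated prevents early reading.** The one safeguard described at handover is the therapist's assurance that he or she will not see the answers. It protects the confidentiality of responses and does not stop a patient reading ahead. Sealing, dating or timed web release is not mentioned either way.

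The sample size (198, or 99 per communication style) and the 10 mm target are not inputs to this check.

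**The case against.** The strongest reply is that holding a form is not reading it. The article does not say whether the form is sealed or carries an instruction to wait, and a journal article commonly leaves such logistics to the full protocol or a manual. Web users may not see the items early. This stands as a limit on the consequence: early reading is possible, not documented. It does not remove the point, because the time of handover and the person responsible are stated procedures, not omissions.

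Several stronger readings are tempting, and the article does not support them.

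- **That concealment is defeated.** The stated aim is to keep patients from knowing too much about the exact contents of the styles. The question discloses none of the statements used, and both treatments are finished by handover, so delivery cannot be affected. The item can reveal the contrast to those who read it, which is a narrower matter.
- **That the needle question is also a leak.** Recruitment of Patients already tells everyone that one procedure penetrates the skin and the other does not. The needle item adds nothing to that.
- **That the completion questionnaire must be moved as well.** Its described items (overall nausea, burden, perceived antiemetic effect) do not reveal the communication factor.
- **That a loss of power can be calculated.** The share of patients reading ahead and the change in their ratings are not given, and even the direction is unknown. Any power figure would rest wholly on assumptions, and a loss is not the only possibility, since the effect could also be inflated.

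**Conclusion.** The point holds in a limited form. The timing is certain from the text: the 10-day form is in the patient's hands with 0 of 5 primary-outcome days complete. That the form contains the question naming the communication contrast is the natural reading but should be confirmed against Figure 3. If it does, a stated procedure works against the concealment and patient blinding that the article claims for the contrast on which the trial was sized.

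The step to a biased result needs three further things: that patients read ahead, that they infer the factor, and that their ratings change. None is documented, and neither size nor direction can be estimated from the article. The change is worth making because it removes an avoidable risk at little cost, not because bias has been shown.

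**What to change.** In Data Collection, replace therapist handover of the 10-day questionnaire with dispatch by the study coordinator, through the post or e-mail route already used for the baseline questionnaire and the diary. It should arrive around day 10, with the web version released on the same timing. If the whole form cannot be moved, hold back at least the communication-style item until the diary entry for the last of the five primary-outcome days is complete. Dispatch around day 10 is preferable because it also protects the rest of the daily expectation series. The completion questionnaire can stay as it is.

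Recruitment is described as ongoing, so record for each patient how and when the form was delivered, and bring in the change for all allocation groups at a hospital at the same time, so that it is not tied to allocation. Results can then be described by handover method, bearing in mind that this is not a randomized comparison.

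Cost: one extra mailing per patient, a difference in delivery between earlier and later patients, and possibly a slightly lower return than with a form given in person. The reminder already planned about 1 to 2 weeks after an expected response covers the last of these.
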